### Recruitment and randomization

Informed consent will be obtained from all women before study entry. Breast and gynecological cancer patients registering for a new chemotherapy regime at the National Centre for Tumour Diseases (NCT) Heidelberg and the Community Hospital Karlsruhe will be informed by flyer, their treating oncologist, or nursing staff about the CONGO study. Then, a CAM-trained nurse will approach the potential participant, briefly inform her about the study and ask her if she would like to have further information. Those agreeing will be provided with details of the study verbally and in written form via the study information leaflet. Patients who agree to participate will be asked to sign the consent form. After informed consent, baseline assessments will be conducted. The nurse will assert if the potential participant has a strong preference to receive the CAM nursing intervention and allocate her into the observational part of the study if applicable. All other participants will be allocated into the randomized part.

The CAM-trained nurses will randomize the study participants using *randomizer.at*, which is an online central randomization service. Participants will be stratified by cancer center (NCT Heidelberg/Community Hospital Karlsruhe) and stage of cancer (curative treatment/palliative treatment), and then randomly allocated at a ratio of 1:1 to the intervention or control arm of the randomized part of the trial. Blocked randomization with varying block sizes will assure that the numbers in the arms are balanced, while the nurses are not being given the possibility to deduce the next allocation. Further, allocation concealment will be ensured, as the randomization service does not release the code for the randomization done by the CAM-trained nurse administering the intervention. Thus, it will be assured that the recruiter has no knowledge about the random sequence and hence cannot influence participants due to possible bias.

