### Sample size and power considerations

Sample size was calculated for the global quality of life (Items 29 and 30 of EORTC-QLQ-C30) and was based on a two-group comparison using Student’s t-test because no reliable estimate of the correlation between repeated measures was available. Following the recommendation by Cocks *et al*. [36], a difference of 10 points between the randomized groups was considered clinically important (that is, ‘smallest medium difference’). This difference corresponds to a standardized effect of d = 0.4 according to Cohen. To detect d = 0.4 with a power of 1 - β = 80% using a two-sample t-test at a two-sided significance level α = 5%, a total of 200 patients in the randomized arms (100 per arm) will be required. The sample size calculation was performed using nQuery Advisor V7.0. We expect the power of the main statistical analysis to be higher than 80% because repeated measurements will be taken into account and the analysis will be additionally adjusted for relevant covariates such as HRQoL at baseline.

We assume that 40% of the patients have no or no strong preference and thus will be randomized. About 60% of the patients are assumed to have a strong preference for the CAM intervention. Therefore, we need to include 200 patients in the randomized arms (100 per arm) and we expect to include about 300 patients in the observational arms. Assuming up to 15% of patients may not have primary outcome data available, the sample size was adjusted to a total of 236 patients in the randomized arms (118 per arm) and about 354 patients in the observational arms.

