A linear mixed model will be used to compare HRQoL under chemotherapy between the two randomized groups from treatment start to long-term follow-up (T1 to T4). This model takes into account the hierarchical structure of the data with repeated measurements nested in patients (that is, patients will be included as random effects in the intercept). Fixed effects will include treatment (usual nursing care versus complex nursing care intervention on CAM), the time of measurement (T1 to T4), the interaction of treatment and time, as well as the HRQoL baseline scores at T1, and the stratification variables stage of cancer (non-metastatic versus metastatic) and study centre (university hospital versus community hospital). Because the measurements are not equidistant in time, an unstructured covariance matrix will be estimated. For the main effect of treatment, the null hypothesis of no difference in group averages will be tested at the two-sided significance level of α = 0.05. Differences between short-term and long-term effects will be assessed by the interaction of treatment and time. The primary analysis will be performed for all randomized patients according to the intention-to-treat principle. As sensitivity analysis, the analysis will be repeated in the per protocol set, excluding patients with major protocol violations. Because longitudinal mixed models make use of the missing at random assumption, no imputation will be used to handle missing data in the primary analysis. However, sensitivity analyses will be conducted to assess the impact of missing data (for example, omitted measurements at some time point) by various approaches, including for example the ICA-r method (imputation according to reasons for missingness [62]), the last observation carried forward, and multiple imputation. Model fit will be assessed by visual inspection of residual plots. Descriptive analyses of secondary endpoints will be performed. All estimates will be presented with 95% confidence intervals. External validity will be assessed by comparing the randomized with the non-randomized patients. The comparison of the observational group will thereby facilitate the applicability of the results. The central part of the second analysis step is, thus, to assess whether treatment effects observed in the randomized patients are comparable with those observed in the two observational arms. If there are measurable differences between these two groups with regard to prognostic factors, the effect of these differences will be examined using propensity score methods. Propensity scores will be determined that reflect the patients’ preferences.

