The shift from inpatient to outpatient cancer treatment has increased awareness of patients’ self-care strategies and also of their significant others (SOs) including family members and close friends [74,75]. Cancer has become a family disease affecting not only the individual with the cancer diagnosis, but also involving their SOs who often are experiencing high levels of distress [76] while accompanying and supporting their loved one going through the treatment stages and adjusting to a new life situation [77]. A strength of the current study is the consideration of patients’ SO, whose QoL will be assessed T1, T3, and T4; and who will be interviewed during the process evaluation to gain a better understanding about their perceptions on the cancer patient’s experiences with the complex nursing care intervention on CAM. The interventions have been primarily composed for the patient receiving chemotherapy, and therefore exclude couple-based methods; however, some of these home-based interventions can be administered by the SOs (for example, preparing the tea, conducting the massage). Thus, the current study will provide further information in highlighting if the shared CAM use contributes to bonding and improvements of QoL in cancer patients’ SOs [74,75].

A further strength of the CONGO study is the interprofessional aspect, which takes into account the collaboration between health professionals in the design of the study as well as in the composition of the complex nurse-led intervention. To our knowledge, this is one of the first nurse-led CAM intervention studies in Germany that can assess nurses’ relevant contribution in promoting HRQoL during cancer therapy.

Another unique aspect of the CONGO study is patients’ choice of the study arm. Due to high interest and prevalence of CAM in cancer populations, we expect that 60% of participants will decide for the intervention and will therefore be allocated into the observational study arm. This study arm will be analyzed descriptively and will be used to assess the external validity of the study results. However, it will be a challenge to recruit enough participants for the randomized arm.

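### The second analysis step compares treatment effects with an observational usual-care arm to which the protocol assigns no expected patients and no clear route of entry

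*Protocol article*

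**What the plan says.** The Data analysis section of the protocol article describes two steps. The first is the classical analysis of the randomized patients. The central part of the second is "to assess whether treatment effects observed in the randomized patients are comparable with those observed in the two observational arms". The same section adds that "External validity will be assessed by comparing the randomized with the non-randomized patients", and that propensity scores reflecting preference will be used if prognostic factors differ.

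On who enters the observational part, the article says different things in different places:

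- **Sample size and power considerations:** 40% of patients have no strong preference and are randomized. "About 60% of the patients are assumed to have a strong preference for the CAM intervention". No share is given for a strong preference for usual care.
- **Discussion:** "we expect that 60% of participants will decide for the intervention", and these women form the observational study arm, in the singular.
- **Recruitment and randomization:** the nurse places a woman in the observational part if she strongly prefers to receive the CAM intervention. All others go to the randomized part.
- **Design of the study:** women with strong preferences, without limit to CAM, are given their choice.
- **Control group:** usual-care participants are described for both the randomized and the observational part.

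**The concern.** A treatment effect is a contrast between CAM and usual care. To say whether the effect among women who chose is like the effect among women who were randomized, the observational part must contain women on usual care. Three sections leave that group without planned patients, and one of them, read literally, also closes the way in: a woman who strongly prefers usual care would be randomized. Two other sections assume that the group exists.

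At stake is what can be concluded from 354 of 590 patients. The observational part is meant in large measure to support external validity, and the analysis called central to that purpose either cannot be computed or would be very imprecise. The planned propensity scores do not solve this. They adjust for measured differences between women with and without a preference, but they cannot supply a missing comparator.

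**Working it through.** **Inputs.** From Sample size and power considerations: "a difference of 10 points between the randomized groups was considered clinically important"; "This difference corresponds to a standardized effect of d = 0.4 according to Cohen"; two-sided 5% level, 80% power; up to 15% without primary outcome data; 40% randomized, about 60% preferring CAM. From Recruitment and randomization: 1:1 allocation. The implied SD is 10/0.4 = 25 points.

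**The plan's own figures reproduce.**
- The two-sample t-test needs 99.08 per arm, rounded up to 100 per arm or 200 in total (power 0.804 at 100 per arm).
- Allowing for missing data: 200/0.85 = 235.3, giving 236 (118 per arm).
- Total: 236/0.40 = 590. Observational part: 590 × 0.60 = 354 enrolled, and 200/0.40 × 0.60 = 300 evaluable.

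**Observational usual-care patients implied.** 590 × (1 − 0.40 − 0.60) = 0. The 354 are exactly the women assumed to prefer CAM, so no observational treatment effect can be estimated on these figures.

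**If some women do choose usual care.** The article gives no share, so the shares below are assumptions. With m evaluable usual-care choosers among 300, and 100 + 100 evaluable randomized patients, unadjusted:

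SE of the difference between the two effects = 25 × √(1/100 + 1/100 + 1/m + 1/(300 − m)); half-width of the 95% CI = 1.96 × SE.

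| Assumed share of observational patients | m | 95% CI half-width (points) | Power for a 10-point difference in effects |
|---|---|---|---|
| 0% | 0 | not estimable | – |
| 5% | 15 | 14.7 | 27% |
| 10% | 30 | 11.7 | 39% |
| 25% | 75 | 9.5 | 54% |
| 50% | 150 | 8.9 | 59% |

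Example at 5%: 25 × √(0.02 + 0.0667 + 0.0035) = 7.51, and 1.96 × 7.51 = 14.7.

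The randomized part alone contributes 1.96 × 25 × √0.02 = 6.9 points, so no number of observational controls brings the half-width below that without adjustment. A half-width of 10 points requires 1/m + 1/(300 − m) = (10/49)² − 0.02 = 0.0216, or m of about 58, which is 19% of the 300.

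**Effect of baseline adjustment.** With an assumed baseline correlation of 0.5, each half-width is multiplied by √(1 − 0.25) = 0.866. This gives 12.7 at 5%, 10.1 at 10% and 8.2 at 25%.

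**The contrast that the planned numbers do support.** Randomized CAM (about 100 evaluable) versus chosen CAM (about 300): 1.96 × 25 × √(1/100 + 1/300) = 5.7 points unadjusted, or 4.9 with the same adjustment.

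**The case against.** The strongest reply is that the 60% is an approximate planning figure and not an entry rule. The Background speaks of preferences for receiving or not receiving the intervention, the design section offers choice, and the Control group section describes observational controls. A few such women may therefore be recruited. This stands: a reader might infer that the observational usual-care arm is certain to be empty, and the article does not support that. It supports only that the arm has no stated size and that its sections disagree about entry.

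A reader might also infer that the external-validity aim has no basis at all. That goes too far. The article plans comparisons of women with and without a preference, exploration of characteristics associated with preference, and propensity score methods; none of these needs an observational control arm. The design has other stated purposes too, such as limiting disappointment bias in the randomized comparison and recruiting more patients.

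A third tempting inference is that comparing randomized with non-randomized women would produce a false preference effect. With half of the former and all of the latter on CAM, a 10-point CAM effect would give a gap of 10 × (1.0 − 0.5) = 5 points. That follows only if outcomes are pooled across treatments, and the article does not say that they will be.

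Finally, the observational part is described as a descriptive analysis, and all estimates are to carry 95% confidence intervals, so imprecision would be visible and no power target applies. This is fair, and the power figures are only illustrative. But a descriptive effect still needs a comparator. Nor is this a detail left to a fuller document: the article commits to a comparison that its own numbers and allocation rule do not provide for.

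**Conclusion.** The concern holds as an internal contradiction with a consequence for analysis. On the plan's own figures the observational usual-care arm has zero expected patients, and the recruitment rule as written gives no route into it, so the effect comparison named as central to the second step has no internal comparator. If 5% to 10% of observational women nevertheless chose usual care, the difference in effects would be known to within about ±15 to ±12 points. Even at 25% it would be about ±9.5, close to the full 10-point important difference. Failure to see a difference would then be weak evidence that the effects are comparable.

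These widths rest on SD 25 as implied by the plan, 15% missing data, no covariate adjustment, and assumed shares; baseline adjustment would narrow them moderately. The primary randomized analysis is unaffected. External validity can still be addressed through patient characteristics and outcomes under CAM, but not through comparability of treatment effects unless enough women choose usual care.

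**What to change.** 1. Reconcile Design of the study, Recruitment and randomization, Control group, Sample size and power considerations, Data analysis and Discussion on whether women who strongly prefer usual care enter the observational part. State how many are expected.
2. Define the main outcome contrast of the second step as randomized-CAM versus preference-CAM patients on global HRQoL, adjusted for the primary model's covariates and the planned propensity score. Describe it as the difference in outcome under CAM between women with and without a strong preference.
3. Make any outcome comparison of randomized with non-randomized women within treatment. Comparisons of characteristics can stay as planned.
4. Make the comparison of treatment effects conditional on a pre-stated minimum number of evaluable observational usual-care patients, justified by the resulting confidence interval width. Otherwise drop it.

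The analysis changes are changes of wording and add no patients or assessments. The cost is a narrower claim: external validity would rest on patient characteristics and outcomes under CAM, not on the treatment effect itself.

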
### Quality assurance

The study is planned in accordance with the German data protection law and ICH/GCP guidelines. External monitoring and consultations with an advisory board will ensure patient safety and highest possible data quality. Monitoring visits will be conducted on a regular basis by independent qualified study nurses of the Department of General Practice and Health Services Research, University Hospital Heidelberg. This monitoring will include pre-study-visits and monitoring visits using standard operating procedures with monitoring of complete eCRFs of at least 10% of the patients included and of core and safety data of the remaining patients. Furthermore, study nurses will check the provision of the interventions in both study sites on a random basis.

All instruments will be piloted to assure readability and limit missing item response. Survey instruments will be provided by the coordinating centre (Department of General Practice and Health Services Research) to minimize printing error or layout variation. The coordinating centre will be responsible for scanning of all questionnaires from both study sites, for query management and data consistency check. This study is supported by an external advisory board including experts/representatives of CAM, clinical pharmacology, oncology, study methodology, nursing science, statistical science and the patient perspective.

## Discussion

The CONGO study is the first prospective partially randomized patient preference trial investigating the impact of a nurse-led intervention involving both clinic and home-based CAM use in breast and gynecologic cancer patients undergoing chemotherapy in two outpatient cancer services. The findings from this study will add to the growing body of evidence of the effectiveness of CAM interventions for individuals with cancer, by testing several aspects relevant for the implementation of patient-centered models of integrative healthcare: (1) patients will receive cancer care including CAMs and individual counseling on CAM by oncology nurses; (2) patients’ preference to receive the CAM intervention will be considered; (3) patients’ empowerment resources will be activated in the initial and following individualized counseling interviews, by receiving standardized CAM instructions and an additional information booklet including evidence-based CAM for home use; (4) The effect of the intervention will be measured on HRQoL and a range of other physical and psychosocial symptoms; (5) Sustainability and long-term effects of this intervention will be assessed by follow-up; (6) A thorough process evaluation will provide explanation on succeeding or impedimental factors impacting concomitantly on the process of the intervention.

The majority of breast and gynecologic cancer patients receive adjuvant or neoadjuvant chemotherapy, which may help to cure their cancer, or prolong life, but also affects their HRQoL due to treatment side-effects or psychosocial concerns [63]. Research consistently demonstrates that cancer patients have a high interest in complementing their conventional cancer treatment by using CAMs [3,5], and some integrative cancer centers have incorporated patients’ preference in providing counseling and methods reflecting a holistic treatment approach [18]. There is, however, a lack of research investigating the effects of such integrated services on a range of patient-centered outcomes in cancer patients treated with chemotherapy [64]. Previous randomized trials mostly investigated the efficacy of one CAM therapy on primary and secondary outcomes [65-68]. Likewise, other effectiveness studies, including nonpharmacologic interventions focused on investigating cognitive or educational programs, however, excluded CAM therapies [69,70] not knowing if patients applied CAM nevertheless. The current study aims to address this aspect by supplying patients in the control group with a patient diary to collect data related to physical and psychological symptoms as well as other supportive therapies patients may apply. While many intervention studies with cancer patients aimed to target cancer-related fatigue (CRF) [71-73], the CONGO study is designed to investigate if cancer patients’ and their significant others’ quality of life will be affected by the complex CAM nursing intervention.

In contrast to efficacy studies, the current effectiveness study will consider several elements when analyzing participants’ HRQoL. The intervention targets common symptoms of patients undergoing chemotherapy. To address these symptoms, a range of CAM interventions will be administered to the patient in the outpatient centre at each cycle of chemotherapy. Some of these CAM interventions are already part of the clinics’ nursing standards [20]; however, they have not yet been standardized and evaluated. In the current study, the patients will also receive counseling on how to apply some of these CAM interventions at home between cycles. Plus, patients will receive an evidence-based information booklet on different CAM interventions as well as contact sources on other external CAM providers in case they prefer to pursue the wide CAM spectrum further on. As a chemotherapy regimen lasts very long (for example, 24 weeks) the patient will visit the outpatient clinic every 3 to 4 weeks that is, 6 to 8 times. It is likely that the patient builds a relationship with the assigned CAM nurse caring for her, which might also add to improvements in HRQoL. In the randomized group, we can account for potential confounders, and analyze the primary and secondary outcomes, but we cannot explain which single element of the interacting intervention agents has the highest impact on changes in HRQoL.

The shift from inpatient to outpatient cancer treatment has increased awareness of patients’ self-care strategies and also of their significant others (SOs) including family members and close friends [74,75]. Cancer has become a family disease affecting not only the individual with the cancer diagnosis, but also involving their SOs who often are experiencing high levels of distress [76] while accompanying and supporting their loved one going through the treatment stages and adjusting to a new life situation [77]. A strength of the current study is the consideration of patients’ SO, whose QoL will be assessed T1, T3, and T4; and who will be interviewed during the process evaluation to gain a better understanding about their perceptions on the cancer patient’s experiences with the complex nursing care intervention on CAM. The interventions have been primarily composed for the patient receiving chemotherapy, and therefore exclude couple-based methods; however, some of these home-based interventions can be administered by the SOs (for example, preparing the tea, conducting the massage). Thus, the current study will provide further information in highlighting if the shared CAM use contributes to bonding and improvements of QoL in cancer patients’ SOs [74,75].

A further strength of the CONGO study is the interprofessional aspect, which takes into account the collaboration between health professionals in the design of the study as well as in the composition of the complex nurse-led intervention. To our knowledge, this is one of the first nurse-led CAM intervention studies in Germany that can assess nurses’ relevant contribution in promoting HRQoL during cancer therapy.

Another unique aspect of the CONGO study is patients’ choice of the study arm. Due to high interest and prevalence of CAM in cancer populations, we expect that 60% of participants will decide for the intervention and will therefore be allocated into the observational study arm. This study arm will be analyzed descriptively and will be used to assess the external validity of the study results. However, it will be a challenge to recruit enough participants for the randomized arm.

The logistic implementation of the CONGO study presents challenges in recruiting the two centers and the healthcare staff involved. Several meetings, involving mutual exchange visits of the involved nursing staff have taken place to facilitate the planning and coordination of the procedure of the study, and to find solutions for recruiting enough patients for the randomized arm. During these pre-study meetings, how the study participants can be recruited without any interruptions for the outpatient clinic routine has been elaborated, as well as how to care for and treat the study participants of the different study arms - with and without receiving the intervention. The organization of the study requires a flexible schedule of the CAM-trained nurses, as they have to inform the patients about the study, collect their informed consent, conduct the initial counseling and follow-up interviews, as well as conduct the intervention while the patient receives chemotherapy. In addition, it will be expected that the CAM-trained nurse cares about the data collection and documents the implementation of the intervention in an electronic case report file (eCRF).

In summary, the CONGO study has been designed to evaluate the effectiveness of an intervention involving CAM therapies and counseling on CAM as complementing the supportive care of breast and gynecologic cancer patients undergoing chemotherapy. It is hypothesized that this intervention increases HRQoL and clustered symptoms over the chemotherapy regimen and follow-up in this outpatient population, and that this is highly relevant to know in the context of promoting and advancing integrative cancer care/clinics.

